5.5.2 Treatment allocation

Randomization will be into one of four study groups:

High Frequency – Manual stimulation: Women randomly allocated to this group will receive 3 acupuncture treatments in the 7 days prior to menses and 1 acupuncture treatment in the first 3 days of menses. Stimulation will be provided by manual acupuncture, achieving DeQi upon needle insertion. Subsequent stimulation based on practitioners differential diagnosis. Needles will be retained for 20-30 minutes

High Frequency – Electro acupuncture stimulation: Women randomly allocated to this group will receive 3 acupuncture treatments in the 7 days prior to menses and 1 acupuncture treatment in the first 3 days of menses. Stimulation will be provided by Electro-Acupuncture, achieving DeQi upon needle insertion. Subsequent stimulation will be using a 2/100Hz waveform for 20-30 minutes.

Low Frequency – Manual Stimulation: Women randomly allocated to this group will receive 3 acupuncture treatments in the 3 weeks prior to menses (1/week) and 1 acupuncture treatment in the first 3 days of menses. Stimulation will be provided by manual acupuncture, achieving DeQi upon needle insertion. Subsequent stimulation based on practitioners differential diagnosis.Needles will be retained for 20-30 minutes

Low Frequency – Electro acupuncture stimulation: Women randomly allocated to this group will receive 3 acupuncture treatments in the 3 weeks prior to menses (1/week) and 1 acupuncture treatment in the first 3 days of menses. Stimulation will be provided by Electro-Acupuncture, achieving DeQi upon needle insertion.Subsequent stimulation will be using a 2/100Hz waveform for 20-30 minutes.

5.5.3: Withdrawal procedures

If a participant wishes to withdraw from the trial they will be immediately removed from treatment. The most recent menstrual pain diary will be used and they will be requested to complete an SF-36.

If a participant withdraws during intervention they will not be replaced however if they withdraw post randomization but prior to the first treatment they will be replaced.

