## 5.2 Screening for eligibility:

Initial screening will be undertaken over the phone by the researcher. Women who meet the eligibility criteria and are interested in joining the study will be met in person if they are located in Auckland or further information will be given via post or email if in Wellington. Prior to trial entry but post consent potential participants will be asked to fill in a menstrual pain diary that will be used to prevent recall error and validate that the participants do have maximum/peak pain greater than or equal to 3/10 and that this pain occurs just prior too, or in the first three days of menses. If these participants are eligible and are randomized then this data will become the baseline data.

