## 7.2 Study assessments

The menstrual pain diary will be used to assess primary and secondary endpoints at baseline and at the end of every menstrual period during the 3 month study period. Follow-up pain diaries will also be collected at 1, 6 and 12 months post trial completion.

The SF-36 will be assessed at baseline and then at 1 month post trial completion.

Patient satisfaction with the trial will be assessed at the end of the trial with an exit questionnaire given after the final acupuncture treatment.

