# 8. Data Collection

The primary investigator, [name], will be responsible for collection of these outcomes at baseline, after each subsequent menstrual period during the trial phase and then again at one, six and twelve months post trial completion.

Baseline data includes age, ethnicity, height, weight, age of menarche, onset of dysmenorrhea, length of menstrual cycle, length of menstrual period, smoking status, alcohol consumption, baseline analgesic usage and self reported dysmenorrhea symptoms and severity. A 5 point Likert scale will assess prior belief in acupuncture’s effectiveness.

*Primary outcome measure:*

Numerical rating scale (NRS) for pain. Each subject will keep a menstrual diary provided by the researcher. This will note the day of menses, average and maximum pain per day on an 11 point NRS with 0 being no pain and 10 being the worst pain imaginable. NRS is used in preference to VAS as it is comparable (59) but has a higher compliance rate, is easier to use and fits the compact format of a menstrual diary (60). The primary endpoint is a 20% difference in NRS rated average pain severity between groups.

*Secondary outcome measures:*

Secondary outcome measures which will be captured by the menstrual diary are duration of menstrual pain (hours), menstrual characteristics (flow, clots), painkillers taken (type, dosage, number of doses), non pharmacological interventions (heat,rest) and secondary symptoms of dysmenorrhea (headache, vomiting etc).

HRQoL will be recorded by the Short Form Health Survey (SF-36) at two time points; baseline and at the one month follow-up. The SF-36 has been shown to be valid and reliable across a range of populations (61,62) and has shown suitability for use in dysmenorrhea (63).

An exit questionnaire will be used to determine patient satisfaction with the different interventions and examine which components of the consultation and treatment sessions were important.

*Quality assurance:*

Quality assurance measures on needling technique and point selection will be carried out on practitioners during the study period by using an independent acupuncturist to check point selection and location at least once for each practitioner. Needling technique will be measured using a newly validated tool, the AcuSensor (64).

*In-depth interviews:*

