# 9. Statistics and Data Analysis

## 9.1 Sample Size calculation:

This trial is designed to demonstrate a 20% difference in average pain intensity between groups as measured by the Numeric Rating Scale (NRS). Based on previous study data (65) a standard deviation of 1.3 units on a pain scale was used. An alpha of .05 and power of 90% gives a total sample size of 60 women. Previous studies (35,65) have had relatively low loss to follow-up (~10%) therefore a sample size of 68 women will be used to account for the predicted loss to follow-up of 10%.

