## 9.2 Proposed Analysis:

For the data from the clinical trial a range of data analysis techniques will be undertaken including simple descriptive statistics; two way repeated measures ANOVA for NRS pain scores and SF-36 scores. Regression analysis with GLM will be used to examine factors influencing NRS scores, analgesic intake, secondary symptoms and non-pharmacological therapies. Non-parametric data such as analgesic intake, presence of secondary symptoms and usage of non-pharmacological therapies will be analysed by Mann-Whitney U-test.

Data from the in-depth interviews will be transcribed verbatim from the digital recording by the researcher. NVIVO will be used to manage the transcribed data and digital recordings. Thematic analysis will be used to identify emergent themes from the data.

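### Section 5.5.3 in effect carries a withdrawn woman's last pain diary forward, which biases the comparison if pain is falling and withdrawal or its timing differs between arms

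*Protocol*

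**What the plan says.** Protocol Section 5.5.3 (Withdrawal procedures) gives the rule for a woman who leaves: "The most recent menstrual pain diary will be used and they will be requested to complete an SF-36". The same section provides for replacement only of women who leave before any treatment; women who leave later stay in the trial without a substitute.

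Three other sections determine which diary is the most recent one:

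- Section 5.2, on the diary kept before randomisation: "If these participants are eligible and are randomized then this data will become the baseline data".
- Section 7.2, on when diaries are collected: "at baseline and at the end of every menstrual period during the 3 month study period", with further diaries at 1, 6 and 12 months after the trial.
- Section 8, on the outcome itself: "The primary endpoint is a 20% difference in NRS rated average pain severity between groups".

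Section 9.2 plans a "two way repeated measures ANOVA for NRS pain scores and SF-36 scores" and names no other way of handling missing diaries. Section 9.1 expects some loss: "a sample size of 68 women will be used to account for the predicted loss to follow-up of 10" per cent. Sections 7.2 and 8 schedule the SF-36 at baseline and at one month after the trial; Section 5.5.3 asks for one at withdrawal and does not say how it will be analysed.

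**The concern.** A diary already collected needs no special rule to count at its own time point. A rule that the latest diary is to be used for a woman who has left makes sense only if it stands in for the diaries she did not complete. That is last observation carried forward, applied to the primary outcome.

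The method assumes that pain stays where it was when she left. Treatment runs over three cycles and is expected to reduce pain, so the carried value will tend to be too high. The error is largest for women who leave in the first cycle, because their only diary predates treatment.

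Two results are at stake. The first is the comparison of arms: if more women leave one arm, or leave it sooner, that arm's pain is overstated relative to the other. The second is the before-after change. Section 2 asks whether the manualised protocol gives a positive outcome, and Section 6.2 provides no control group, so that change is distorted even when withdrawal is perfectly balanced.

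**Working it through.** **Which diary is carried**

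| When she leaves | Most recent diary | Consequence |
|---|---|---|
| Before first treatment | Baseline | Replaced (5.5.3) |
| After first treatment, before first on-trial period ends | Baseline (5.2, 7.2) | Scored at pre-treatment pain |
| After first or second on-trial period | That cycle's diary | Later change is not counted |

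**Planned loss.** The protocol's step from 60 to 68 reproduces: 60 / 0.9 = 66.7, rounded up to 67, then to 68 for four equal groups of 17. Ten per cent of 68 is 6.8, so about 7 women. The two frequency schedules have 2 × 17 = 34 women each.

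**Formula.** With no true difference between schedules,

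bias = (leavers in A − leavers in B) / 34 × improvement not yet reached at the last diary.

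**Assumptions** (none given in the protocol): true improvement by cycle 3 of 1, 2 or 3 points, and how the 7 losses split. The main illustration also assumes that every leaver has only a baseline diary.

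- 5 v 2: 3/34 = 0.088, times 1, 2, 3 = 0.09, 0.18, 0.26 points.
- 7 v 0: 7/34 = 0.206, times 1, 2, 3 = 0.21, 0.41, 0.62 points.

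**False-positive rate.** The SD comes from Section 9.1 ("a standard deviation of 1.3 units on a pain scale was used"). I simulated a t-test at cycle 3, 34 v 34, two-sided 5% level, no true difference, 20,000 runs. This is a simplification of the planned repeated measures ANOVA.

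| Split | Last diary | Bias for 1, 2, 3 points | Rejection rate |
|---|---|---|---|
| 4 v 3 | Baseline | 0.03, 0.06, 0.09 | 4.7%, 3.4%, 2.1% |
| 5 v 2 | Baseline | 0.09, 0.18, 0.26 | 5.4%, 5.7%, 6.3% |
| 6 v 1 | Baseline | 0.15, 0.29, 0.44 | 6.6%, 11%, 16% |
| 7 v 0 | Baseline | 0.21, 0.41, 0.62 | 9%, 20%, 34% |
| 7 v 0 | Cycle 1, one third of the gain assumed reached | 0.14, 0.27, 0.41 | 6.5%, 12%, 20% |

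If pain does not change, the bias is zero for every split.

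**Before-after change.** If all 7 leavers are scored at baseline, the overall improvement is understated by 7/68 = 0.103 of its size: 0.10, 0.21 or 0.31 points for true improvements of 1, 2 or 3, whichever arms the women came from.

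**The case against.** The strongest reply has four parts.

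- **Carry-forward is inferred.** The sentence does not name the method or the visits to which the diary would apply, and an analysis plan not at hand may say more. This is fair, but the rule stands in the protocol, carry-forward is its natural reading, and if another use was meant the sentence needs rewording anyway.
- **The baseline case is narrow.** Women who leave before treatment are replaced, and those who leave after an on-trial period carry a treated-cycle diary. This stands. The main illustration is the worst case for timing.
- **Nothing predicts unequal withdrawal.** Both schedules give four treatments per cycle and 12 in all, and Section 9.1 predicts only total loss. So imbalance cannot be called likely. It remains possible: Section 2 treats the acceptability of more frequent treatment as an open question.
- **The effect is small at moderate splits.** This stands too: 5 v 2 barely moves the error rate, and near-balanced loss makes the test slightly conservative.

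A reader might go further and infer that copied values make the error term too small and the confidence intervals too narrow. That is not shown. Leavers stay high while others improve, which adds spread. In a simulation with 34 v 34, SD 1.3, an assumed within-woman correlation of 0.5 and about 10% loss in each arm, the within-woman error mean square moved from 0.845 to 0.79, 0.83 and 0.91 for falls of 1, 2 and 3 points. It can go either way.

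A reader might also infer that the SF-36 taken at withdrawal replaces the one-month value. Section 5.5.3 only requests the form; its role is unstated.

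**Conclusion.** The point holds in conditional form. The protocol fixes a carry-forward rule for the primary outcome and offers no alternative. The rule biases the comparison of arms when pain is falling and withdrawal or its timing differs, and it distorts the before-after change even when withdrawal is equal. The bias may create a difference, or shrink or hide a real one.

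At the planned loss it ranges from under 0.3 points at a 5 v 2 split to about 0.6 points at the extreme 7 v 0 split with a 3-point improvement. These sizes rest on the assumed improvement, split and timing; only the 10% loss, the SD and the group sizes are the protocol's.

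It would be tempting to say that any unequal withdrawal produces a false treatment difference, or to quote larger gaps in withdrawal. The documents support neither: the bias vanishes if pain is stable, and larger gaps would generally need more loss than Section 9.1 plans. Nor can the bias be judged against a stated detectable difference in points, because the protocol does not say of what value the 20% is taken. This is a should-fix point.

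**What to change.** Replace the diary rule in Section 5.5.3, and align Section 9.2 with it:

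1. State that no diary is carried forward.
2. Analyse all observed diaries from all randomised women in a likelihood-based mixed model for repeated measures, with baseline pain as a covariate.
3. Distinguish stopping treatment from leaving the study, and keep collecting the scheduled diaries and the one-month SF-36 from women who agree. This matters most for first-cycle leavers, who otherwise contribute no diary after baseline.
4. State that an SF-36 completed at withdrawal is not used as the one-month value.
5. Add one sensitivity analysis for informative dropout.

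The cost is a change of wording, a few follow-up contacts and slightly more analysis work. No extra visits are needed. The change should be settled before outcome data are examined.

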# 2. Study Objectives

The primary aim of this project is to examine the effect of changing frequency and type of stimulation on the symptoms of primary dysmenorrhea.

The specific questions that this project address are:

1. Does using a manualised protocol based on current clinical experience provide a positive outcome with symptoms of primary dysmenorrhea?
2. What extent do differing frequencies of treatment and types of stimulation contribute to that effect?
3. Is acupuncture, especially in more frequent treatments, an acceptable intervention for participants ?
4. Does TCM acupuncture change study participants perceptions of health and illness with respect to dysmenorrhea ?
5. What other components of the acupuncture treatment are important to study participants ?

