## 5.3 Consenting participants

For those that consent and have an eligible menstrual pain diary a trial entry form will record baseline clinical data as well as demographic characteristics. Randomisation will occur after trial entry form completed.

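### Replacing women who withdraw between randomisation and the first session can bias the frequency comparison and lose refusals that bear on acceptability

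*Protocol*

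**What the plan says.** Section 5.5.3 treats withdrawals in two ways. Once sessions have begun: "If a participant withdraws during intervention they will not be replaced". Before that: "if they withdraw post randomization but prior to the first treatment they will be replaced". On data from women who withdraw it says: "The most recent menstrual pain diary will be used and they will be requested to complete an SF-36". It does not say whether this covers a woman who has been replaced, or whether her replacement takes the next number in the schedule or the arm just vacated.

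Section 5.5.2 sets the schedules. Before menses, the high-frequency arms have "3 acupuncture treatments in the 7 days prior to menses" and the low-frequency arms "3 acupuncture treatments in the 3 weeks prior to menses (1/week"). Both add one session early in menses.

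Section 5.3 places randomisation in time only by "Randomisation will occur after trial entry form completed"; no cycle day is fixed. Section 2, question 3, asks: "Is acupuncture, especially in more frequent treatments, an acceptable intervention for participants".

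**The concern.** Frequency is one of the two components that Section 1.2 makes the main focus of the trial, and Section 6.2 confirms that there is no control group. The contrasts between arms carry the randomised evidence.

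A woman must know her schedule to book her visits, so she may leave because of it before session 1. The rule then recruits another woman, who by staying has accepted the schedule. If the first woman drops out of the analysis, the arm has been selected after randomisation on something linked to the allocation. The two schedules need not put off the same number of women, or the same kind.

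Question 3 is exposed too. The exit questionnaire follows the final treatment (Section 7.2), and interviews are offered to women who complete the trial (Section 1.1). Neither is aimed at a woman who refuses her schedule before session 1. Section 5.4 logs ineligible women and those who decline after initial contact, and no section asks for pre-treatment withdrawals to be reported by arm.

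**Working it through.** **1. Does the sample size need the rule?** Section 9.1 goes from 60 to 68 women for 10% loss. 60 / 0.90 = 66.7, so 67, and the next multiple of four arms is 68. The plan's figure is reproduced, and losses are already allowed for without replacement.

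**2. A yardstick for size.** Section 9.1 gives SD 1.3, alpha 0.05 (taken as two-sided) and power 90%. For 30 v 30 the detectable difference is 1.3 × (1.960 + 1.282) × sqrt(2/30) = 1.09 points. The standard error of the contrast with all 34 v 34 is 1.3 × sqrt(2/34) = 0.32 points.

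**3. Wait from randomisation to session 1.** Section 4.3 allows cycles of 21 to 35 days. Let L be cycle length, with days counted from onset of the baseline period. Assume the first low-frequency session falls on day L−21 to L−14, and the first high-frequency session on day L−7 to L−3, so that three still fit. Assume also that a woman randomised after her window has closed waits one more cycle. The randomisation days are assumed, since the protocol fixes none.

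| L | Randomised on day | Wait, low (days) | Wait, high (days) | High minus low, midpoints |
|---|---|---|---|---|
| 28 | 5 | 2 to 9 | 16 to 20 | +12.5 |
| 28 | 12 | 0 to 2 | 9 to 13 | +10 |
| 28 | 16 | 19 to 26 | 5 to 9 | −15.5 |
| 21 | 5 | 0 to 2 | 9 to 13 | +10 |
| 21 | 8 | 13 to 20 | 6 to 10 | −8.5 |
| 35 | 5 | 9 to 16 | 23 to 27 | +12.5 |
| 35 | 16 | 0 to 5 | 12 to 16 | +11.5 |

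The wait differs by frequency arm in every row, but its direction depends on the day of randomisation.

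**4. Possible shift in the frequency contrast.** Suppose the women replaced are left out. Let rH and rL be the proportions replaced in the high- and low-frequency arms, and d the difference in pain score between those who leave and their replacements. Shift = (rH − rL) × d. None of these inputs is in the protocol.

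- rH 5%, rL 0%, d 0.5: 0.05 × 0.5 = 0.025
- rH 10%, rL 3%, d 1: 0.07 × 1 = 0.07
- rH 15%, rL 5%, d 2: 0.10 × 2 = 0.20
- rH 20%, rL 5%, d 2: 0.15 × 2 = 0.30
- rH 10%, rL 10%, any d: 0

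The range is about 0.03 to 0.3 points, or 2% to 28% of 1.09. The top case means about 7 of 34 high-frequency women replaced (0.20 × 34 = 6.8). The last case gives zero only because d is taken as the same in both arms; equal rates with different kinds of women leaving would still shift the contrast.

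**The case against.** The strongest reply is that the rule does no harm by itself. A woman who leaves before session 1 and returns no more diaries is missing whether or not someone is enrolled after her. Bias needs two further things: that she is left out of the analysis, and that such women differ between arms. The protocol states neither, its sentence on using the latest diary could be read to include her, and analysis populations are often left to the SAP. This stands in part. It makes the bias conditional, and it means that deleting the rule is not enough without diaries. It does not rescue the rule: filling places with women who stay invites the exclusion, and for a woman not yet treated the latest diary would normally be the baseline one, which holds no outcome.

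The sizes are also assumed throughout, and even the largest is slightly below one standard error (0.32 points). That stands. A bias does not average out as sampling error does, but nothing here shows it to be large.

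Four stronger readings are tempting, and the documents do not support them.

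- **That the replaceable window is about two weeks longer in the high-frequency arms.** This holds for randomisation soon after menses in a 28- to 35-day cycle. It reverses for day 16 of a 28-day cycle, and from day 8 of a 21-day cycle.
- **That the comparison is no longer randomised.** Allocation stays random; the comparison is open to selection only under the conditions above.
- **That the blocked sequence is broken.** Enrolling a replacement through the next number is compatible with the text.
- **That electro-stimulation reveals the arm.** None has been given before session 1. What matters is knowledge of the schedule.

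**Conclusion.** The point holds in conditional form. Section 5.5.3 ties replacement to an event after randomisation whose likelihood can depend on the frequency arm, through the schedule itself and through the wait to session 1. The frequency comparison can be biased if the women replaced are excluded and differ in number or kind between arms. The direction is unknown. The assumed range is roughly 0.03 to 0.3 NRS points, and the shift is zero if withdrawals are alike across arms.

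For question 3, the rule risks losing refusals of a schedule from view. Replacement does not prevent them from being counted, but nothing in the protocol requires it.

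This is a defect in a stated rule, beyond missing detail. It should be settled before enrolment: later analysis cannot recover diaries that were never requested, or undo places filled outside the random sequence.

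**What to change.** In Section 5.5.3, delete the replacement rule. If numbers must be kept up, state that extra women enter only through the next unused number in the randomisation schedule and never take a vacated arm. Add that:

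- every randomised woman stays in the primary analysis in her allocated arm, whether or not she had a session;
- women who withdraw before the first session are asked for the scheduled diaries;
- pre-treatment withdrawals, with reasons where given, are reported by arm as an acceptability result for question 3.

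The cost is a change of wording and some diary follow-up; the 68 women already allow for 10% loss. The downside is slight dilution by untreated women. If 5% of each arm had no sessions and showed no difference by frequency, a true contrast of 1.09 points would be seen as about 0.95 × 1.09 = 1.04.
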